### Rationale of the intervention program

During the New Life(style) program pregnant women in the intervention group receive individually tailored advice. The personal counsellor is a source of information, making the participants aware of the fact that they themselves can influence their weight during pregnancy, but also after delivery. By providing regular guidance following the principles of Problem Solving Treatment for primary care (PST-pc) the counsellor is also a supervisor and coach for the pregnant women. PST is an evaluated, practical psychological intervention method for helping people to gain a sense of control over their difficulties [20]. PST consists on the following elements: 1) increasing one's knowledge; 2) enhancing one's capability to define behaviors in need of change; 3) learning to seek solutions for problems or to set goals to improve or preserve healthy behavior; and 4) emphasizing positive experiences to increase self-confidence [21].

### Content of the counselling sessions

Each counselling session is structured in a uniform way (see Table 1). During the first visit the counsellor talks about weight gain during pregnancy and the distribution of this 'extra' weight among different tissues. After this, the IOM guidelines are introduced and the dependence of healthy weight gain during pregnancy on pre-pregnancy body mass index is discussed. Weight and height is assessed and pre-pregnancy BMI is calculated, after asking for pre-pregnancy weight, in order to categorize women in pre-pregnancy BMI-groups: underweight, normal weight, overweight or obese.

### Weight gain charts

For each pre-pregnancy BMI-group the minimum, mean and maximum weight gain recommendations of the IOM are incorporated in weight gain charts as lines that reflect the accumulative amount of kilograms a women can gain per week, until 40 weeks of gestational age. The women receive a chart, depending on the BMI-group they belong to. On this individual chart weight changes are plotted every time participants of the intervention group visit the counsellor (see Figure 2). Women whose weight changes are within appropriate ranges are informed that they are gaining the expected amount of weight; those gaining too little or those who gain more than recommended are told so.

### Lifestyle

During the remaining time of the first session, but also during follow up sessions, weight gain patterns of the women in relation to their lifestyle is discussed: "how to eat healthy and how to optimise physical activity in order to be able to be in charge of your own weight". Focussing on the relation between energy intake and energy expenditure is an important component of the intervention program. The level of physical activity is assessed by means of the shortened version of the IPAQ [22]. A global assessment of energy intake is done by means of a short questionnaire of the Dutch Nutrition Centre [23] so that the counsellor can give immediate feedback on individual, daily physical activity and nutrition.

Recent studies argue the need for pregnant women to remain physically active during pregnancy, in the absence of contra-indications, because of the beneficial health effects for both mother and child [24]. The information and feedback that the counsellors provide with regard to physical activity are therefore based on the widely accepted recommendations of the American Centers for Disease Control and Prevention, which promote 30 minutes of at least moderate intensity activity on 5 or all days of the week [25]. Guidelines for pregnant women of the Dutch Nutrition Centre constitute the basis of the nutritional part of the counselling sessions [23].

### Goals

The primary goals of the intervention program with regard to physical activity are to provide information and guidance to optimise daily physical activity during pregnancy and to take away common misconceptions about physical activity and exercise during pregnancy (e.g. "exercising is dangerous", "a lot of rest is good for pregnant women"). To accomplish maintenance of a healthy physical activity pattern or to optimise individual physical activity when women don't meet physical activity guidelines; safe, enjoyable, accessible and feasible physical activities are discussed on the individual level. To prevent injuries because of being untrained, previously sedentary women are advised to increase physical activity in small steps and with regard to activities of moderate intensity and low impact, such as cycling instead of taking a bus, or walking during lunch breaks. The wellbeing of the unborn child is always taken into account; counsellors will talk about possible contra-indications for physical activity. The dietary intervention focuses on optimising energy-intake, adjusting energy-intake to physical activity and to take away misconceptions about nutritional requirements during pregnancy (e.g "the need to eat for two" [26]). Special attention is given to decreasing intake of high-fat foods, such as fast food items and sugar-containing soft drinks.

Subsequently, the counsellor makes a plan with the women who don't meet the weight gain, physical activity or dietary guidelines, but also with those who foresee difficulties later in pregnancy. In this plan, goals with regard to physical activity and/or nutrition are incorporated as explicitly as possible, in order to make it easier to achieve them (e.g. by describing the type, frequency, intensity and duration of planned physical activities). Counsellors complete a form after each session in which they register weight gain pattern, the content of each conversation and personal goals that have been set. During subsequent visits, the content of the previous session is evaluated and, if necessary, plans are adjusted.

### Counselling session 5

The fifth and last counselling session, at 8 weeks postpartum, is done by phone. The focus of this session is mainly on recovery from delivery, breast feeding and how to take care of the new baby, in combination with regular physical activity and/or healthy nutritional patterns.

### Counsellors

Two counsellors are responsible for the execution of all counselling sessions with participants in the intervention group. They have a background in physical activity or remedial education and were trained before the start of the study to provide individual feedback on the modules, according to the earlier described standardized counselling protocol. After the counsellors studied related literature and the protocol, the training was performed with ten pregnant women. The conversations with these ten pregnant women allowed the counsellors to become acquainted with the protocol and the target group. The conversations were taped so that they could be studied by the research team, consisting of an epidemiologist, a health scientist, a gynaecologist and the two counsellors. It was checked whether the counsellors adhered to the protocol and problems which the counsellors ran across were discussed. During the study all sessions are taped as well, and regular follow-up sessions with the research team are organised in order to discuss taped conversations.

### Co-interventions and compliance

The participating midwives are asked not to take part in other research programs in order to prevent possible disturbing effects from co-interventions. Compliance to the intervention programme is assessed by registering the number of treatment sessions attended by the participants. Furthermore, the content of each session is registered by the counsellors in individual files of the participants in the intervention group.

### Measurements

Participants in both the intervention and control group are invited for six measurement appointments in the period during and after pregnancy. The baseline measurement is at 15 weeks of pregnancy. Data are collected at: 15, 25, and 35 weeks of pregnancy and at 8, 26, and 52 weeks after delivery. At these occasions the research assistants perform anthropometrical measurements in all midwifery practices and register the primary outcome measures. Blood samples are collected in five of the eight participating practices by trained assistants; in the other three practices the assistants are not schooled for intravenous punctures and consequently no blood samples can be collected. Each assistant is permanently linked to one or more practices, so that participants are measured by the same person at each occasion. All participants receive questionnaires by ordinary mail one week before each measurement appointment. They are asked to complete the questionnaires and hand these in when they visit the research assistant for a measurement appointment. The assistant personally checks the questionnaires for missing data. The following measures are assessed:

### Primary outcome measures

#### Body weight and BMI

Body height is measured on bare feet by means of a wall-mounted height scale (SECA 206), with an accuracy of 0.1 cm. Calibrated electronic scales (SECA 888) are used to determine body weight of the participants in underwear and pants, with an accuracy of 0.1 kg. Both weight and height is measured twice, and the mean value of the two measurements is computed and used to calculate individual body mass index (BMI, kg/m^2^) at 26 and 52 weeks after pregnancy. Pre-pregnancy BMI is based on self reported pre-pregnancy weight.

### Skinfold thickness and percentage body fat

A Harpenden calliper is used to assess skinfold thickness of the following four skinfolds: biceps, triceps, subscapular and suprailiac, according to the method described by Weiner and Lourie [27]. All skinfolds are assessed twice. A mean value of the two is computed. In case the two measurements of a skin fold differ more than 1.0 mm, the skin fold is measured a third time and the mean value of the three values is calculated.

### Secondary outcome measures

#### Physical activity and nutrition

Physical activity is assessed with the Short Questionnaire to Assess Health enhancing physical activity (SQUASH). This questionnaire has been validated in a population of Dutch employees [28]. At 15 and 35 weeks of pregnancy and 26 weeks after delivery all participants wear an accelerometer for 4 consecutive days (actigraph, GT7164). Accelerometer data are used as additional, objective data on physical activity. With regard to nutrition, questions have been developed for the purpose of this study, concerning the amount of times per week that participants have breakfast, lunch and dinner. Also the frequency of eating snacks is assessed. The validated Dutch Eating Behaviour Questionnaire (DEBQ) is used to identify nutrition related problems such as restrained, emotional, and external eating [29].

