### Blinding

All anthropometric outcome measures are assessed by independent examiners unaware of group allocation. Participants cannot be blinded for the intervention, but are asked not to reveal information about their treatment to the examiners. The key of coding concerning group assignment is only known by the programmer of the database that is used during the study.

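### Physical activity is assessed by self-report in unblinded women, only one arm of which is coached on its reported activity; the accelerometer comparison should be pre-specified beside the SQUASH, and a SQUASH-only difference called reported activity

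*Protocol article*

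**What the plan says.** **Instruments.** The section on physical activity and nutrition, under secondary outcome measures, names a questionnaire first: "Physical activity is assessed with the Short Questionnaire to Assess Health enhancing physical activity (SQUASH"). It adds a device: "At 15 and 35 weeks of pregnancy and 26 weeks after delivery all participants wear an accelerometer for 4 consecutive days". It then gives the device its place: "Accelerometer data are used as additional, objective data on physical activity".

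**How self-report is collected.** The Measurements section states: "All participants receive questionnaires by ordinary mail one week before each measurement appointment". There are six such appointments. The women complete the forms themselves, and an assistant checks them for missing items.

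**Blinding.** The Blinding section states: "Participants cannot be blinded for the intervention, but are asked not to reveal information about their treatment to the examiners". Masked assessment is stated for one class of outcome only: "All anthropometric outcome measures are assessed by independent examiners unaware of group allocation".

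**What the intervention arm receives.** In the counselling sessions, according to the Lifestyle section, "The level of physical activity is assessed by means of the shortened version of the IPAQ". The counsellor gives feedback on the answers at once, against a 30-minute activity recommendation. Under Goals, women who miss the guidelines, or expect difficulty later, draw up a plan with explicit activity goals, and later sessions review it.

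**Analysis.** The Statistical analyses section lists physical activity levels as the fourth of five effect domains. It names no instrument for that domain and does not say what follows if the SQUASH and the accelerometer disagree.

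**The concern.** For a self-completed questionnaire, the participant is the assessor. Here the assessor knows the allocation. In one arm only, she has also been questioned about her activity, told the target, given feedback and helped to set goals before she fills in the next outcome form. This can change what she counts as activity and what answer she thinks is wanted, whether or not her activity has changed.

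Any resulting difference between arms is a bias, not noise. A larger sample does not reduce it; it only makes the same bias more often significant. The trial could then report that counselling raised activity when only reporting had changed. The article already has a measure that does not depend on the women's answers, collected from all of them, but gives it a supplementary place and no stated part in the conclusion.

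**Working it through.** **1. Order of events** (sections Randomisation, Intervention, Measurements, Physical activity and nutrition)

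| Time | Counselling (intervention arm only) | Questionnaires (both arms) | Accelerometer (both arms) |
|---|---|---|---|
| 10–14 weeks | women told their arm | – | – |
| 15 weeks | – | yes | yes |
| 18, 22 weeks | sessions 1, 2 | – | – |
| 25 weeks | – | yes | no |
| 30 weeks | session 3 | – | – |
| 35 weeks | – | yes | yes |
| 36 weeks | session 4 | – | – |
| 8 weeks postpartum | session 5 | yes | no |
| 26 weeks postpartum | – | yes | yes |
| 52 weeks postpartum | – | yes | no |

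Three sessions come before the 35-week report and all five before the 26-week postpartum report. Counselling thus falls between baseline and these outcome reports, so adjusting for the baseline SQUASH cannot remove a change in reporting that counselling causes. At both times a device reading exists for the same women, with a 15-week value to adjust for. If the SQUASH is in every mailing, its other three post-baseline reports have no objective counterpart.

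**2. Size: illustration only**

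The article gives no SQUASH scale, variance or reporting bias, so there is no figure of its own to reproduce here. The one input taken from it is the number evaluable in the sample size section: 275 × (1 − 0.20) = 220, or 110 per arm. Everything else is assumed: SD 200 min/week, no true effect, a net over-reporting δ in the counselled arm relative to control, and one unadjusted comparison at two-sided 5%.

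- Standard error of the difference: 200 × √(2/110) = 27.0 min/week.
- Probability of a significant difference: Φ(δ/SE − 1.96) + Φ(−δ/SE − 1.96).

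| Assumed net over-reporting | In SD units | δ/SE | Probability of p < 0.05 |
|---|---|---|---|
| 0 | 0 | 0 | 0.05 |
| 15 min/week | 0.075 | 0.56 | about 0.09 |
| 30 min/week | 0.15 | 1.11 | about 0.20 |
| 60 min/week | 0.30 | 2.22 | about 0.60 |

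In SD units, which need no assumed SD, net biases of 0.1, 0.2, 0.3, 0.4 and 0.5 SD give 0.12, 0.32, 0.60, 0.84 and 0.96. The two calculations agree at 0.3 SD (60/200).

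Only the difference in reporting between arms enters δ. Over-reporting that is equal in both arms cancels.

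**The case against.** The strongest reply is that much of this is inference.

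- **The ranking.** A reader might infer that the SQUASH decides the activity conclusion and prevails if the two measures disagree. The article does not say so. The inference rests on the one word *additional*, which can mean no more than also collected, and the analysis section names no instrument. A fuller protocol or analysis plan may settle it. This stands. What remains is that the article names the questionnaire as the measure and gives the device a supplementary place.
- **The direction of bias.** A reader might infer that over-reporting occurs in one arm and in one direction. Nothing in the article shows this. Controls are also unblinded volunteers who had the aim explained and may over-report. Coaching on what counts as activity could make reporting stricter. The coached form is the IPAQ, not the SQUASH. This stands too, although both forms are self-reports of the same behaviour, and bias in favour of the coached arm remains plausible.
- **The numbers.** The rejection rates rest on assumed inputs and a single unadjusted comparison, whereas the article plans longitudinal regression. They say nothing about how large the bias is in this trial.
- **The device.** A reader might conclude that the accelerometer should replace the SQUASH as the sole lead measure. That does not follow. It covers 4 consecutive days at three of six time points and may miss cycling, which the programme itself gives as an example of promoted activity. A device-only rule could overlook a true effect.
- **The consequence.** Activity is a secondary outcome. The sample size rests on BMI, and the anthropometric measures have blinded examiners.

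None of this answers the core point. A difference seen only on the questionnaire cannot be told apart from a difference in reporting, and the article sets no limit on what may be concluded from it.

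**Conclusion.** The concern holds in a limited form. The article names an unblinded self-report as the physical-activity measure and treats the objective data as supplementary, while only one arm is repeatedly coached on its reported activity. Differential reporting could therefore appear as an effect in the physical-activity domain. It plausibly favours the intervention, but its size and direction are not established.

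The 9%, 20% and 60% figures show only how quickly an assumed bias turns into significance with 110 women per arm; they are not estimates for this trial. The documents do not support a claim that the activity result is already decided by the SQUASH, or that bias has been shown. The consequence is confined to what may be concluded about activity, and the blinded anthropometric outcomes are unaffected.

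**What to change.** - Pre-specify the accelerometer group difference at 35 weeks of pregnancy and at 26 weeks postpartum, each adjusted for the 15-week value, alongside the SQUASH analysis.
- State that an effect on activity level will be claimed only when the accelerometer result supports it, and define support before results are seen.
- State that a difference found on the SQUASH alone will be described as a difference in reported activity.
- Keep and report the SQUASH in full. State the limits of the device (4 days, three of six time points, possible loss of promoted activities such as cycling), and say that a lack of accelerometer difference does not prove no effect.

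The cost is wording and one pre-specified analysis. No new data are needed, because the device is already planned for all participants at these three times. The price is a more cautious claim: a true rise in activity that the device misses would be reported only as a rise in reported activity.

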### Blood samples

In order to study the influence of lifestyle factors on energy homeostasis and weight gain, blood samples are taken intravenously from a subgroup of participants during each measurement. The midwives also take a blood sample from the umbilical cord. Blood is processed and stored at the laboratory of the VU University Medical Centre, so that – after selecting subgroups of normal and high gainers – blood levels of leptin, ghrelin, fasting insulin/glucose, insulin growth factor 1, insulin growth factor binding protein 1 and 3, and cortisol can be measured.

By means of the questionnaires, data are also collected on: perceived health, stage of change with regard to weight management, physical activity and diet according to the model of Prochaska, and behavioral determinants such as attitude, social support, self efficacy with regard to weight management, physical activity and nutrition. Possible confounders that are assessed include: age, age at menarche, education, ethnicity, marital status, smoking behaviour and individual health status, including complications during pregnancy, the duration of labour and possible complications during or after delivery.

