### Statistical analyses

Analyses will be performed to estimate the effect of the intervention on five domains: 1) total weight gain during pregnancy 2) the percentage of women gaining weight above the recommended IOM guidelines; 3) weight retention at six months and one year postpartum; 4) physical activity levels; and 5) behavioral determinants of weight management, physical activity and nutrition.

Longitudinal logistic regression analysis will be used for dichotomous outcome measures, and longitudinal linear regression analyses will be performed for all other outcome measures. In these analyses, the correlation between multiple measurements within one individual is taken into account. The regression coefficient reflects the average difference in the outcome variable between conditions. Possible confounders will be entered into the regression analyses. Confounding will be defined as a change in the regression coefficient of 10% or more. Possible effect modification will be studied as well, defined as a significant (p <0.10) interaction-term between group allocation and the variable concerned. Datawill be analysed according to the intention-to-treat principle and the per protocol principle.

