## Discussion

The New Life(style) intervention program is designed to fill the gaps that currently exist for public health professionals with regard to providing guidance for pregnant women who have difficulties with controlling their weight gain during pregnancy. As a result of the close cooperation with the participating midwife practices in this study, we are able to reach a representative study population of women who are expecting their first child. Furthermore, the counselling sessions of participants in the intervention group and the measurements of all participants are performed in these practices, hereby minimising the burden for women who participate in the study. Because of the personal and repetitive character the New Life(style) program is expected to be a helpful tool to help pregnant women to gain weight within IOM-guideline limits.

Results of the current RCT will improve insight in determinants of weight gain during pregnancy, weight retention after childbirth and in the effectiveness of the intervention program. If the New Life(style) intervention program proves to be an effective tool, a future update of the Dutch and/or international guidelines of midwifery care with the current protocol will be needed. Because of the fact that the counselling sessions in this study are provided by members of the research team, implementation of the New Life(style) protocol in the daily practice of midwifes will then need to receive further attention.

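### Complications of pregnancy, labour and delivery are classed as possible confounders for the effect regressions, although they arise almost entirely after randomisation and should be compared between arms

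*Protocol article*

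**What the plan says.** The questionnaire paragraph at the end of the Blood samples section of the protocol article opens a list with "Possible confounders that are assessed include: age, age at menarche, education, ethnicity, marital status, smoking behaviour" and ends it with "individual health status, including complications during pregnancy, the duration of labour and possible complications during or after delivery". Both arms supply these data: the Measurements section says "All participants receive questionnaires by ordinary mail one week before each measurement appointment".

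The Statistical analyses section then says "Possible confounders will be entered into the regression analyses", and treats a variable as a confounder when it changes the regression coefficient by 10% or more. The same section says "Analyses will be performed to estimate the effect of the intervention on five domains". These are total gain, "the percentage of women gaining weight above the recommended IOM guidelines", weight retention, physical activity, and behavioural determinants.

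The Goals section acknowledges risk within the counselling. It mentions contra-indications to activity and injury in untrained women, and states "The wellbeing of the unborn child is always taken into account". The Discussion says that, should the programme prove effective, "a future update of the Dutch and/or international guidelines of midwifery care with the current protocol will be needed".

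**The concern.** A confounder of a randomised comparison has to precede allocation. Complications and labour duration mostly follow it, and a programme that acts on intake, activity and weight gain could plausibly change them. Treating them as confounders has two consequences.

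- **Bias.** If the programme changes a complication that itself influences weight, adjustment removes part of the programme's effect. If the complication and the weight outcome share other causes, conditioning on it can create a difference between arms that randomisation did not produce.
- **Lost information.** Data that could show whether complications differ by arm are assigned to the covariate side of the model. Dropping them from the model would cure the bias but would not by itself produce a comparison.

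At stake are an unbiased effect estimate and the reader's ability to weigh benefit against harm when the article looks ahead to guidelines.

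**Working it through.** **1. Timing.** The Randomisation section puts notice of allocation at 10–14 weeks of pregnancy, and the Intervention section puts the first session at 18 weeks. Labour, delivery and post-delivery complications all come later. Of complications during pregnancy, only very early ones could come first, and the confounder list does not separate them.

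**2. What the 10% rule does with such a variable.** In a linear model at one time point, unadjusted minus adjusted effect = g × d. Here g is the within-arm association of the complication with the outcome, and d is the difference in complication rate between arms. For a baseline variable, d is chance imbalance. For a post-randomisation event, d may be an effect of the programme, so the rule tends to select the event when the programme has changed it.

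Illustration on BMI, the sample-size outcome: 10% of the 0.8 kg/m² target is 0.08 kg/m². With d = 0.079 (the half-width at a 10% rate in step 5), the rule is met when g is about 0.08/0.079 = 1.0 kg/m². This assumes the unadjusted effect equals the target. The identity is exact for ordinary least squares and only a guide for the longitudinal models.

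**3. Stated outcomes and domains.** The primary outcomes are body weight, BMI and skinfolds. The secondary outcomes are physical activity, nutrition and blood factors. Neither these nor the five effect domains include a maternal, obstetric or newborn health outcome. The guideline domain counts only gain above the recommendation, although the Weight gain charts section has counsellors identify women who gain too little.

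**4. The article's sample size, the source of the 110 per arm.** Inputs: difference 0.8, SD 2.0, two-sided 5%, power 0.80.

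n per group = 2 × (1.960 + 0.842)² × 2.0² / 0.8² = 98.1, so 99. The stated 110 is higher and gives about 84% power. The dropout step reproduces: 220/0.80 = 275. The excess is conservative and has no bearing on this point.

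**5. Precision of a by-arm comparison.** Half-width of the 95% interval for a risk difference at a common rate p = 1.96 × √(2p(1−p)/n). The rates are assumptions, because the article gives none. The last column is power to detect a doubling of the control rate at two-sided 5%.

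| Assumed rate | Half-width, n = 110 | Half-width, n = 137 | Power for a doubling, n = 110 |
|---|---|---|---|
| 2% | 3.7 points | 3.3 points | 14% |
| 5% | 5.8 points | 5.2 points | 29% |
| 10% | 7.9 points | 7.1 points | 55% |
| 20% | 10.6 points | 9.5 points | about 90% |

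Worked line for 10%: 1.96 × √(0.18/110) = 1.96 × 0.0405 = 0.079.

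If an event occurs in none of 110 women, the upper 95% bound is 1 − 0.05^(1/110) = 2.7% (rule of three: 3/110 = 2.7%).

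The 110 is the evaluable number planned at six months postpartum. The number with delivery data could lie between it and the roughly 137 randomised per arm (275/2), hence both columns.

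**The case against.** The strongest reply is that this is a condensed design article. By-arm tables of pregnancy and delivery outcomes are commonly left to a full protocol or analysis plan, and neither is shown. The five domains are also not a complete list of analyses: skinfold thickness is a primary outcome and blood levels are secondary, yet neither appears there. Both points stand, so a reader should not infer that complications have no use other than as confounders, or that nothing on harm will be reported. They do not answer the stated assignment, which places post-randomisation events on a list that feeds the effect models.

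A reader might also infer that the trial will recommend a guideline change whatever the complications. The Discussion does not say that. Its sentence is conditional on effectiveness, it adds that implementation will need further attention, and it is not a decision rule. What remains true is that the condition named is effectiveness alone.

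Nor does the article support a picture of unguarded risk. The programme aims at gain within guideline limits, the charts carry a minimum line, and midwives give usual care to everyone. Newborn size is not mentioned, so no scenario about it can be drawn from the text. The questionnaires are not shown, so it cannot be said that birth weight or gestational age goes unrecorded.

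Finally, a low-powered, self-reported table cannot act as a formal safety test. That is accepted. It argues for descriptive reporting with intervals, and against making a guideline statement hinge on passing such a test.

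**Conclusion.** The point holds as a misassignment in the stated text. Events that arise almost entirely after randomisation are called possible confounders and directed to the effect regressions. No stated effect domain compares them between arms, and the forward-looking guideline sentence refers to effectiveness only.

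The size of any bias cannot be given, because it depends on associations the article does not report. The illustration shows only that the 10% rule could plausibly be met. The precision of the missing comparison can be given: about ±5.8, ±7.9 and ±10.6 percentage points at assumed rates of 5%, 10% and 20% with 110 per arm. The trial can therefore say something about common complications but cannot exclude harm for uncommon ones.

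**What to change.** - In the questionnaire paragraph, remove complications during pregnancy, labour duration and complications during or after delivery from the possible confounders. Limit adjustment to variables fixed before randomisation.
- Report these events by randomised arm among all randomised women with delivery data, with the number of women behind each figure. Give counts, percentages and risk differences with 95% intervals, and a difference in means for labour duration. Label the table descriptive.
- If birth weight and gestational age at delivery are already recorded, put them in the same table.
- Amend the Discussion to say that any guideline statement will be read together with this comparison, and that the trial cannot exclude harm for uncommon events. Quote the half-widths above with their assumed rates.

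The data already come from both arms, so this needs no new visits, staff or participants. The cost is one extra table, with wide intervals and self-reported events.
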